## Methods

### Design

A randomized controlled three-group experimental design was used. First-time mothers (n=204) were recruited from a public hospital in Singapore. Recruited mothers were randomly assigned into any of the three groups: intervention group 1 (receiving the Web-based psychoeducational intervention plus routine care), intervention group 2 (receiving the home-based psychoeducational intervention plus routine care), and the control group (receiving routine care). Research assistant (RA2) who helped with follow-up data collection did not have any knowledge of the treatment allocation of participants, which was completed by another research assistant (RA1).

### Participants

The criteria for inclusion were first-time mothers who: (1) had full-term pregnancy, (2) were 21 years old and older, (3) were able to read and speak in English, (4) had Internet access through a computer or a smartphone, and (5) planned to reside in Singapore for the 6 months post delivery. The exclusion criteria were mothers who: (1) had identified physical or mental disorders (eg, cognitive impairment, schizophrenia, psychosis, or suicidal signs) before and during pregnancy that would hinder their ability to participate in the study, (2) had complicated assisted delivery with 4th degree perineal tear, and/or (3) gave birth to a stillborn child or a child with congenital anomalies or medical complications (eg, pathological jaundice), which required specialized attention in the hospital. A group of participants (15 from each group) were selected to participate in the process evaluation for the purpose of obtaining their opinions and comments on the Web-based, home-based psychoeducational intervention, and routine care.

### Web-Based and Home-Based Psychoeducational Intervention

The Web-based and home-based interventions were developed based on Bandura’s theory on self-efficacy [55], social support, findings from previous literature [38-40,43], and local preliminary studies [40,46,55-61]. Both interventions contain similar intervention contents but with different modes of delivery—Web-based or home visits. Table 1 shows the comparison of protocol of routine care, and Web-based and home-based postnatal psychoeducational interventions.

At 6 weeks post-delivery: Follow-up with the obstetrician; advice on: breastfeeding; PAP smear; intrauterine contraceptive device upon patients’ request; and EPDS for those mothers who have defaulted the 2 weeks appointment	2nd to 4th week after discharge: Weekly telephone calls x 3; reinforce the use of website resources	2nd to 4th week after discharge: Weekly telephone calls x 3; reinforcement of the content covered during home visit; find out new challenges faced by the mothers; and provide individualized support as per mothers’ needs

#### Home-Based Psychoeducational Intervention

Participants assigned to intervention group 2 received periodic care and a home-based postnatal psychoeducational intervention. There was a 1-hour face-to-face psychoeducation via a home visit by a registered nurse (RA1). An educational booklet was also developed based on the one used in the preliminary study [61] with new evidence-based knowledge added, such as mindfulness-based practice and using cold cabbage leaves for managing breast engorgement [61], which were provided to participants before hospital discharge. The main contents in the booklet provided for the home-based intervention were identical to the one from group 1. The contents were validated by an expert panel, consisting of 5 health care professionals (2 professors in Obstetric and Gynecological Nursing, 1 senior consultant in obstetrics, 1 experienced midwife in postnatal care, and 1 postnatal psychologist). There was also a thrice-weekly telephone follow-up to answer mothers’ queries.

### Control Group

Participants assigned to the control group only received the routine care provided by the hospital.

### Sample Size Determination

In similar studies, psychosocial and educational interventions have resulted in a medium effect size on outcomes similar to this study [44,52,62]; hence, the study intervention was regarded to have a medium size effect on outcome variables. On the basis of a power analysis, to achieve a medium effect size of 0.55, using a power of 80% and a significance level of 5% (2-sided), 52 participants would be needed in each group [63]. Although a dropout rate of 30% was reported by a previous study [52] and our preliminary study [46], we anticipated a lower dropout rate of 24% in this study because of better communication channels established with participants (eg, using social media such as WhatsApp to remind participants, follow-up questionnaire conducted through a Web-based survey). Therefore, a minimum sample of 204 (52×3/0.76) participants with 68 in each group was needed. For process evaluation, a purposive sampling of 45 participants (15 from each group) with different posttest 1 self-efficacy scores (5 high, 5 moderate, and 5 low scores from each group) were invited to participate in a process evaluation interviews, or until data saturation was achieved.

### Randomization

A random sequence generator was used to generate three sets with 68 unique random integers in each set that ranged from 1 to 204 without being sorted [64]. Three sets of numbers were randomly assigned for intervention group 1, intervention group 2, or control group, respectively. The blinding of the participant was not possible because of the nature of the intervention. All 204 unique numbers indicating the group were placed in an opaque box. After assessing eligibility and obtaining informed consent, participants were assigned randomly to either of the groups by drawing a number from the box. Participants were reminded that there will be no change of groups after numbers are drawn.

### Outcome Measures and Instruments

The outcome measured included are maternal parental self-efficacy (MPSE), social support, PND, anxiety, satisfaction with postnatal care, and cost related to health care services used postnatally. The instruments used to measure the key variables included Perceived Maternal Parental Self-efficacy (PMPSE), the modified Perinatal Infant Care Social Support (PICSS-modified), Edinburgh Postnatal Depression Scale (EPDS), Anxiety subscale of the Hospital Anxiety and Depression Scale (HADS-A), Ordinal Descriptive Scale (ODS), and Questionnaire on Healthcare Service Utilization (QHSU).

#### Perceived Maternal Parental Self-Efficacy

The PMPSE is a widely used 17-item instrument that measures maternal self-efficacy in the postpartum period. Each item is rated on a four-point Likert scale. The Cronbach alpha values in a previous study and a local study were .91 [65] and .92, respectively [54].

#### Social Support

The modified PICSS includes the Functional Social Support Measuring Subscale (FSSMS) and Structural Social Support Measuring Subscale (SSSMS). The FSSMS is a 16-item subscale used to measure maternal perceived social support [57] with Cronbach alpha values of .80 in a previous study [57] and .76 in a local study [54]. The SSSMS is a 6-item subscale used to measure the structural dimension of an individual’s social network with a Cronbach alpha of .83 in a local study [54].

#### Psychological Well-Being

The EPDS and HADS-A were used to measure mothers’ psychological well-being, including PND and anxiety. The 10-item EPDS has been used to measure PND widely. The recommended cutoff for probable cases of PND is 12 or 13 [66]. The sensitivity and specificity of the EPDS were 68% to 80% and 77%, respectively, and the Cronbach alpha was .88 [67]. The HADS-A is a 7-item instrument that is most commonly used to assess anxiety symptoms [68]. It is rated on a 4-point scale of 0 to 3. The minimum score of 8 determines the presence of anxiety symptoms [69]. The sensitivity and specificity of HADS-A were 93% and 90%, respectively, when it was used for pregnant women from Nigeria [70].

#### Satisfaction With Postnatal Care

The ODS is a 6-point Likert scale for assessing mothers’ satisfaction with the postnatal care they received [46,59].

#### Health Care Service Utilization

The QHSU was used to capture costs related to health care service usage by the mothers postnatally due to maternal- or infant-related health issues at 1 month, 3 months, and 6 months post delivery. The measurement period for the study was from entry into the program until 6 months. The questionnaire was designed by health economy experts from the Singapore Clinical Research Institute.

### Process Evaluation

Semistructured interviews were conducted for exploring the information regarding the strengths, weaknesses, and perceived effects of the interventions, and the mothers’ opinions on the current routine postnatal care provided by the hospital.

### Study Procedure

Data collection commenced after the ethical approval had been obtained. The nurse in charge was contacted to determine the physical and psychological well-being of potential participants. After confirming the inclusion criteria, the participants were approached at the postnatal inpatient wards. Only after obtaining written consent would the mother be recruited into the study. This was followed by a collection of demographic data and baseline data via a self-administered questionnaire before randomization takes place. Outcomes were measured at the following time points for all participants in all three groups: (1) after delivery and before discharge (baseline data), (2) immediately after the intervention (posttest one, at the end of 1 month post delivery), (3) 2 months after the intervention (posttest 2, 3 months post delivery), and (4) 5 months after the intervention (posttest 3, 6 months post delivery).

RA1 made a visit to the hospital regularly to recruit participants and was responsible for informing all participants of their allocated group, and collection of baseline data for all participants. RA1 provided participants in the Web-based intervention group with Web access (individual username and password) for 1 month. For participants assigned to the home-based intervention group, RA1 provided the educational booklet before discharge and arranging home visits at about 5 to 10 days post delivery, as this is the most crucial period for mothers, as well as 3 telephone calls [71].

RA2 was responsible for the Web-based postnatal psychoeducational intervention (eg, providing expert advice in group discussion forums and confidential corner, and 3 reminder phone calls). RA2 was responsible for the collection of all posttest data, including process evaluation interviews.

### Data Analysis

Quantitative data will be analyzed using IBM SPSS version 24 for Windows (IBM Corp). Descriptive statistics such as mean, standard deviation, and range will be used to report continuous data, whereas frequency and percentages will be used for the nominal and ordinal data. Inferential statistics such as ANOVA will be used to analyze the differences of baseline outcomes among the three groups, whereas chi-square tests will be used to compare the sociodemographics among the three groups.

To answer the hypothesis 1, repeated measures ANCOVA, adjusted for confounding variables (eg, age, ethnicity), will be used to test the effects of both interventions on maternal self-efficacy, social support, postnatal depression, and anxiety across four time points. Univariate ANCOVA will be used to test the difference of each of the three outcomes among three groups at each posttest time point by adjusting for confounding factors (eg, baseline data, age, and ethnicity). Chi-square test or Poisson regression will be used to determine maternal satisfaction with the postnatal supportive care at each posttest time points. To answer hypothesis 2, a 95% CI of the mean difference of maternal self-efficacy scores will be calculated. If the lower boundary is more than −5, the hypothesis will be accepted. To address hypothesis 3, we will calculate the base case incremental cost-effectiveness ratios (ICER) of the two intervention groups compared with the control group. We captured the 6-month costs at three posttest time points: (1) health care system perspectives, including service providers that mothers consumed because of maternal and/or neonatal related conditions such as GP clinic, polyclinic, private clinic, hospital out-patient, hospital Accident and Emergency and (2) participant’s out-of-pocket cost of transportation fee for these visits. In addition, fixed costs (also considered health care system perspectives) such as development and implementation of Web-based intervention, delivery of home-based intervention, and training of RAs were also captured. The effectiveness of the intervention on four outcomes (namely self-efficacy, social support, depression and anxiety) will be calculated. The ICERs for each outcome will be plotted in the cost-effectiveness plane to examine the dominance and extended dominance, and then the cost-effectiveness acceptability curves will be generated to demonstrate the cost-effectiveness of the alternatives using difference willingness-to-pay thresholds [72-78].

Qualitative data from the interviews will be analyzed using thematic analysis [79-83]. The audiotaped interview data will be transcribed verbatim by RA2 concurrently with the data collection to capture nonverbal nuances. Transcribed data will be color coded first, which will then be collated to form subthemes, and eventually to form themes [84]. Two investigators will be involved in the analysis process to compare and discuss the codes, subthemes, and themes that are generated and to achieve consensus. Rigor, including credibility, transferability, dependability, and confirmability, will be considered carefully in the study process [85].

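### The hypothesis 1 model makes the pre-randomization baseline one of four outcome levels, and neither of its terms is a clean test of each intervention against control

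*Protocol article*

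**What the plan says.** All of this is in the Methods of the protocol article.

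- **Data Analysis, hypothesis 1.** "repeated measures ANCOVA, adjusted for confounding variables (eg, age, ethnicity), will be used to test the effects of both interventions" on self-efficacy, social support, postnatal depression and anxiety, over four occasions.
- **Study Procedure.** The four occasions are baseline (after delivery, before discharge) and posttests at 1, 3 and 6 months after delivery. Baseline is collected before randomization.
- **Data Analysis, second method.** A univariate ANCOVA compares the groups at each posttest "by adjusting for confounding factors (eg, baseline data, age, and ethnicity".
- **Data Analysis, software.** "Quantitative data will be analyzed using IBM SPSS version 24 for Windows". No SPSS procedure is named.
- **Sample Size Determination.** The aim is "to achieve a medium effect size of 0.55", and "using a power of 80% and a significance level of 5% (2-sided), 52 participants would be needed in each group". On dropout, "we anticipated a lower dropout rate of 24% in this study", after noting 30% in earlier work; 52 per group is raised to 68, or 204 in total.

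**The concern.** The intervention cannot change a score recorded before randomization, so the expected group difference at baseline is zero. Making that score one of four outcome levels leaves two terms to read, and neither fits hypothesis 1, which compares each intervention with control.

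- The **group main effect** averages the zero baseline difference with the three posttest differences, so it understates the effect.
- The **group-by-time term** has (3 − 1) × (4 − 1) = 6 degrees of freedom with three groups and four occasions. It asks whether the profiles differ in any way, not whether Web or home care beats control.

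The same baseline score is then a covariate in the posttest ANCOVAs. The two analyses can disagree, and the text does not say which one settles the hypothesis.

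A further point concerns missing visits. The classical repeated measures procedure in SPSS (GLM) needs complete rows. Run that way, a mother who misses only month 6 also loses her 1-month and 3-month scores.

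**Working it through.** **Inputs from the protocol article:** effect 0.55 SD, two-sided 5%, 80% power, 52 evaluable per group, 24% dropout, 204 randomized (68 per group).

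**Assumptions, not in the article:** the effect is the same at all three posttests; every pair of occasions has the same correlation ρ, taken as 0.3, 0.5 and 0.7; each occasion has SD 1; normal approximation for contrasts.

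**1. The plan's own figure.** n = 2 × (1.960 + 0.842)² / 0.55² = 51.9, so 52 per group. This is reproduced. For dropout, 156 / 0.76 = 205.3 against the stated 204, a difference of no consequence here.

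**2. Dilution of the group main effect.** (0 + 0.55 + 0.55 + 0.55) / 4 = 0.75 × 0.55 = 0.41 SD.

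**3. Power for one intervention against control, 52 per group.** Power = Φ(effect / √(2V/52) − 1.960).

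- Four-level mean including baseline: effect 0.4125, V = (1 + 3ρ)/4.
- Mean of three posttests adjusted for baseline: effect 0.55, V = (1 + 2ρ)/3 − ρ².
- One posttest adjusted for baseline (the planned visit-wise ANCOVA): effect 0.55, V = 1 − ρ².

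At ρ = 0.5 the first gives V = 0.625 and 0.4125 / √(2 × 0.625/52) = 2.66, so power is Φ(0.70) = 76%. The second gives V = 0.667 − 0.25 = 0.417 and 0.55 / √(2 × 0.417/52) = 4.34, so power is Φ(2.38) = 99%.

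**4. Power for the group-by-time term.** With the profile difference (0, 0.55, 0.55, 0.55), the squared deviations from its mean sum to 0.75 × 0.55². For one intervention against control (3 df) the noncentrality is 52 × ½ × 0.75 × 0.55² / (1 − ρ), which is 11.8 at ρ = 0.5. For all three groups (6 df), with both interventions at 0.55 SD, it is 52 × ⅔ × 0.75 × 0.55² / (1 − ρ), which is 15.7 at ρ = 0.5. Both use the F distribution under sphericity.

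| Analysis | ρ = 0.3 | ρ = 0.5 | ρ = 0.7 |
|---|---|---|---|
| Group main effect, four levels | 86% | 76% | 67% |
| Group-by-time, one intervention vs control (3 df) | 67% | 83% | 97% |
| Group-by-time, three groups (6 df) | 70% | 86% | 98% |
| Visit-wise ANCOVA, one posttest | 84% | 90% | 98% |
| Posttest mean adjusted for baseline | 99% | 99% | >99% |

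**5. Missing visits.** 24% of 204 is 49 mothers, leaving 155, or 51.7 per group. Power for 0.55 SD at a single time point is then 79.8%, so the planned 80% is kept.

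**The case against.** **The article condenses a longer plan.** Missing-data rules, analysis sets and the choice of SPSS procedure may sit in a document not shown, and their absence is not held against the plan. The four-level outcome is different: the article states it. One could say that the four occasions describe the design loosely and that baseline would really be a covariate. But Study Procedure counts exactly four occasions with baseline first, and the covariates named for this model are age and ethnicity, while baseline is named only for the visit-wise ANCOVAs.

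**The 76% against 99% comparison takes the least favourable reading.** This is fair. The article does not say that the main effect is the test. Group-by-time is a usual reading of such a design and is not diluted, and the visit-wise ANCOVAs have 84% power or more in the table. The dilution is therefore conditional on which term is read.

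**A reader might infer that a quarter of the sample is sure to be discarded.** The documents do not support that. Listwise deletion is the ordinary reading of the named method, but SPSS MIXED keeps partial data. The 24% is anticipated dropout, already built into 68 per group. A mother with no posttest adds little to any model; the method itself wastes only the data of mothers with some posttests, and their number is not given.

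**A reader might also infer a definite bias.** Its size depends on an assumed dropout mechanism. In simulations with a true effect of 0.55, ρ = 0.5 and about 26% to 28% dropout tied to low earlier scores, completers-only estimates ran from 0.43 to 0.51 when the link held in the control group only, and were 0.51 to 0.52 when it held in both arms. Under a similar control-only mechanism the visit-wise ANCOVAs gave 0.55, 0.52 and 0.50. Nothing in the article says that dropout works this way. Bias is possible, not shown.

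**Conclusion.** The point holds in this form and should be fixed. As written, the hypothesis 1 model treats a pre-randomization score as an outcome, the companion ANCOVAs treat it as a covariate, and the text does not say which analysis or term decides.

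Read through the main effect, the treatment effect loses a quarter of its size, and at assumed correlations of 0.5 and 0.7 power falls below the planned 80%. Read through group-by-time, there is no dilution, but the test is an omnibus one and at a correlation of 0.3 its power is also below 80%. Both terms are weaker than the baseline-adjusted posttest mean at every correlation tried. These figures rest on a constant effect, equal correlations and 52 complete cases per group; only the factor of three quarters is free of the correlation.

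On missing visits, the harm is wasted partial data and possible bias. It is not a shortfall against planned power.

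**What to change.** Make the hypothesis 1 analysis of each of the four scale outcomes one likelihood-based mixed model, fitted with SPSS MIXED:

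- outcome: the three posttest scores, using all mothers with at least one posttest;
- fixed effects: group, time, group × time, baseline score (and baseline × time), age and ethnicity;
- covariance: unstructured over the three posttests;
- contrasts: Web minus control and home minus control for hypothesis 1, and Web minus home for hypothesis 2, with the deciding contrast and time point (or the mean over posttests) named in advance.

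The visit-wise ANCOVAs can stay as supportive analyses and a completers-only analysis as a sensitivity analysis.

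The cost is a change of wording and a little more analysis work in the package already chosen. No new data are needed. The article reports follow-up as complete and projects data entry and analysis for March to June 2018, so the change should be recorded and dated before any group comparison is run.

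### If all six satisfaction categories are analysed as they stand, the named tests ignore their order (chi-square) or overstate the standard error (Poisson), so power is lost

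*Protocol article*

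**What the plan says.** Under Satisfaction With Postnatal Care, the instrument is described in one sentence: "The ODS is a 6-point Likert scale for assessing mothers’ satisfaction with the postnatal care they received". Its name, given under Outcome Measures and Instruments, is the Ordinal Descriptive Scale (ODS).

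Under Hypotheses, a higher level of satisfaction in both intervention groups than in control is listed as one part of hypothesis 1.

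Under Data Analysis, the test is: "Chi-square test or Poisson regression will be used to determine maternal satisfaction with the postnatal supportive care at each posttest time points". The same section recognises ordinal data as a type, but only for descriptive reporting by frequencies and percentages. It mentions no dichotomisation, cut-point, robust variance, or rank or ordinal method for this outcome.

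Under Sample Size Determination, "the study intervention was regarded to have a medium size effect on outcome variables", with a standardised effect of 0.55, and "52 participants would be needed in each group" before allowance for dropout.

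**The concern.** The hypothesis concerns a shift up an ordered scale. A chi-square test on the six categories gives the same p-value however the categories are arranged, so it spends its degrees of freedom on patterns that the hypothesis does not concern. Poisson regression treats the rating as a count and, with its default variance, sets the variance equal to the mean. A bounded 1-to-6 rating generally varies less than that, so the standard error is too large and the test too cautious.

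At stake is the satisfaction part of hypothesis 1: a real improvement of the size the trial was planned around could go undetected in data able to show it.

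**Working it through.** **1. The plan's own figure.** Inputs from Sample Size Determination: effect 0.55 SD, two-sided 5%, power 80%.

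n per group = 2 × (1.96 + 0.84)² / 0.55² ≈ 51.9, so 52, as stated. With 24% dropout, 52 × 3 / 0.76 = 205.3 against the stated 204 (68 × 0.76 = 51.7 per group). The design reproduces to within two participants, so 52 per group is used below.

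**2. Chi-square and Poisson against a rank test, 0.55 SD shift.** The article gives no ODS distribution, so four control shapes were assumed. A latent normal shift of 0.55 SD was cut into six categories, with 2,000 simulated trials per shape and two groups of 52. The Wilcoxon test stands in for the unadjusted proportional-odds model, of which it is the score test. Power in %:

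| Assumed shape | Wilcoxon | Chi-square, 6 categories | Loss | Chi-square, top two v rest | Loss | Poisson, model variance | Poisson, robust variance |
|---|---|---|---|---|---|---|---|
| Symmetric | 75.6 | 47.8 | 27.8 | 56.2 | 19.4 | 30.4 | 78.1 |
| Uniform | 73.8 | 48.8 | 25.0 | 60.9 | 12.9 | 61.8 | 74.2 |
| Skewed high | 72.7 | 44.9 | 27.8 | 54.0 | 18.7 | 6.9 | 73.2 |
| Very skewed | 64.4 | 36.7 | 27.7 | 40.3 | 24.1 | 0.8 | 64.4 |

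With three groups of 52, Kruskal-Wallis against six-category chi-square gives 79.4 v 49.4, 77.8 v 49.6, 74.0 v 45.0 and 68.6 v 39.5, losses of 28 to 30 points. With all 68 per group retained, the two-group figures are 79% to 86% for Wilcoxon and 53% to 62% for chi-square.

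**3. A second route, by odds ratio.** Assumed control distribution 3/5/10/22/35/25%, 52 per group, 3,000 or 4,000 runs. Repeat runs agreed to within about 4 points. Power in %:

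| Common odds ratio | Rank test | Chi-square, 6 categories | Top two v rest | Poisson, model variance | Poisson, robust variance |
|---|---|---|---|---|---|
| 2 | 50 | 25 | 39 | 4.5 | 47 |
| 2.5 | 72 | 44 | 56 | 11 | 67 |
| 3 | 86 | 62 | 71 | 20 | 82 |

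Losses against the rank test are 24 to 28 points for six-category chi-square, 11 to 16 for the top-two split, and 3 to 5 for Poisson with robust variance.

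**4. Poisson standard error.** The model takes the variance of a group mean as mean/n where it is in fact variance/n, so the ratio of standard errors is √(mean/variance):

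- Uniform: √(3.50/2.92) = 1.09
- Symmetric: √(3.50/1.45) = 1.55
- Distribution in step 3: √(4.56/1.606) = 1.68
- Skewed high: √(4.72/1.46) = 1.80
- Very skewed: √(5.14/1.06) = 2.20

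**5. False positives.** With no true difference and 52 per group, the two-group rejection rate was 2.0% to 4.6% for six-category chi-square and 0.0% to 3.4% for model-based Poisson, against a nominal 5%.

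**The case against.** The strongest reply is that the article does not say that all six categories, or the raw score, enter the test. Chi-square paired with Poisson regression is a familiar choice for a binary outcome: compare proportions, then estimate an adjusted relative risk. On that reading the six-category figures and the standard-error ratios do not apply. This stands as a possibility, which is why the point is conditional. It does not remove the point: no split is stated, and a top-two split still loses about 11 to 24 points.

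It is also fair that Poisson's weakness here lies in the variance setting. With robust variance on the raw score, its power is close to the rank test. The article states no robust variance, but an unseen analysis plan may.

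Four stronger readings are tempting and are not supported:

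- *That the adoption case depends on satisfaction.* Under Principal Findings, the condition is that the Web program is as effective as, and more cost-effective than, the home program; greater satisfaction is listed as a consequence of adoption. The hypothesis 2 rule uses self-efficacy only, and the cost-effectiveness ratios use self-efficacy, social support, depression and anxiety.
- *That the tests could produce false claims of benefit.* Step 5 shows rejection rates below the nominal level.
- *That chi-square hides the direction of any difference.* The planned frequencies and percentages would show it beside the test; the cost is in power.
- *That offering two tests is itself a fault.* A rule for choosing between them is a detail that an article commonly leaves to the full protocol or analysis plan.

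**Conclusion.** The point holds in conditional form. If the six categories are analysed as they stand, both named tests suit the outcome poorly: chi-square loses about 24 to 30 points of power at 52 per group, and model-based Poisson standard errors are about 1.1 to 2.2 times too large. If the rating is split at the top two categories, the loss is about 11 to 24 points. If Poisson is run on the raw score with robust variance, little is lost.

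These sizes rest on assumed rating distributions and on an effect of 0.55 SD, or odds ratios of 2 to 3, applying to satisfaction. The chi-square loss was large under every shape tried. The Poisson loss depends strongly on shape, from about 12 points (uniform) to nearly all the power (very skewed).

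One part of hypothesis 1 is affected and the other outcomes are not. This is a cheap improvement of lower severity, held with moderate confidence because the coding of the ODS is not stated.

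**What to change.** Replace the satisfaction sentence under Data Analysis with one method that uses the order: proportional-odds (ordinal logistic) regression of the ODS rating on group at each posttest, adjusted for the covariates that section already names (age and ethnicity, and a baseline rating if one was collected). Report common odds ratios with 95% CIs for Web v control, home v control and Web v home.

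If a high/low split is also reported, fix the cut before analysis and use Poisson regression with robust standard errors for that binary outcome only.

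The cost is one sentence and a check of the proportional-odds assumption. The sample and data collection do not change. The Results section puts completion of data entry and analysis after the article's follow-up, so the change is still open; because all follow-up data had been collected by August 2017, record that it was made before satisfaction was compared by group.
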